### 3 STUDY OBJECTIVES AND ENDPOINTS

#### 3.1 Phase 1 Objective(s)

##### 3.1.1 Primary Objectives

- To assess the safety and tolerability of D-1553 single agent and in combination with [REDACTED] in subjects with advanced or metastatic solid tumors with KRASG12C mutation
- To determine the DLT, MTD and RP2D of D-1553 single agent and in combination with [REDACTED] in subjects with advanced or metastatic solid tumors with KRASG12C mutation

##### 3.1.2 Secondary Objectives

- To evaluate the PK of D-1553 alone and in combination with [REDACTED] in subjects with advanced or metastatic solid tumors with KRASG12C mutation
- To preliminarily evaluate the antitumor activity of D-1553 alone and in combination with [REDACTED] in subjects with advanced or metastatic solid tumors with KRASG12C mutation

#### 3.2 Phase 1 Endpoints

##### 3.2.1 Primary Endpoints

- Type, incidence, severity (graded by NCI CTCAE, v5.0), attribution and timing of AEs
- Incidence of DLTs

##### 3.2.2 Secondary Endpoints

- PK parameters (AUC0-t, AUCinf, MRT, Cmax, tmax, Cmin, t1/2, Vdss/F and CL/F) of D-1553 [REDACTED]
- ORR (CR + PR), DCR (CR + PR + SD), PFS and DOR, evaluated by RECIST, v1.1

#### 3.3 Phase 2 Objective(s)

##### 3.3.1 Primary Objective:

- To assess the antitumor effect of D-1553 single agent and in combination with [REDACTED] targeted therapy in subjects with advanced or metastatic solid tumors with KRASG12C mutation.

### **3.3.2 Secondary Objectives:**

- To assess the safety and tolerability of D-1553 in subjects with advanced or metastatic solid tumors with KRASG12C mutation
- To evaluate the PK of D-1553

## **3.4 Phase 2 Endpoints**

### **3.4.1 Primary Endpoint**

- ORR (CR + PR)

### **3.4.2 Secondary Endpoints**

- DCR (CR + PR + SD), PFS, DOR, evaluated by RECIST, v1.1 and OS
- Type, incidence, severity (graded by NCI CTCAE, v5.0), attribution and timing of AEs
- Based on PK data obtained in this study as well as PK data obtained from other studies, a population PK analysis will be performed to characterize pharmacokinetic parameters (Clearance (CL), Volume of distribution (V)) and evaluate the effect of extrinsic and intrinsic factors to support proposed dosing regimen

## 4 INVESTIGATIONAL PLAN

### 4.1 Overall Study Design

This is a phase 1/2, open label study of D-1553 single agent and in combination with [REDACTED] [REDACTED] targeted therapy to assess the safety and tolerability, identify the MTD and RP2D, evaluate the PK properties and antitumor activities in subjects with advanced or metastatic solid tumor with KRASG12C mutation. The study is divided into Phase 1 and Phase 2 portions. Phase 1 will consist of 2 parts: Phase 1a (dose escalation) and Phase 1b (dose combination). Subjects will take D-1553 orally on an empty stomach every day in a 21 or 28day treatment cycle. The study treatment will be administered until disease progression, withdrawal of consent, unacceptable toxicity or discontinuation from the study for other reasons.

#### 4.1.1 Phase 1a (Dose Escalation)

Phase 1a will start to evaluate 4 sequential cohorts administered with once -daily oral doses of D-1553 (see Table 4-1): Cohort 1 (150 mg once -daily), Cohort 2 (300 mg once -daily), Cohort 3 (600 mg once -daily) and Cohort 4 (1200 mg once daily). An additional 3 sequential cohorts administered with twice- daily oral doses of D-1553 will also be evaluated: Cohort 5 (400 mg twice- daily; total 800 mg daily), Cohort 6 (600 mg twice- daily; total 1200 mg daily) and Cohort 7 (800 mg twice- daily; total 1600 mg daily). After the safety of Cohort 3 has been determined, the dose escalation of the twice daily administered cohorts (Cohorts 5 to 7) will be conducted in parallel to the once- daily administered Cohort 4.

**Table 4-1 Dose Escalation Cohorts For Phase 1a**

| Cohorts (once daily)  | Cohort 1   | Cohort 2   | Cohort 3   | Cohort 4    |                    |                    |
|------------------------------|-------------------|-------------------|-------------------|--------------------|--------------------|--------------------|
| Dose                  | 150 mg once daily | 300 mg once daily | 600 mg once daily | 1200 mg once daily |                    |                    |
| Cohorts (twice daily) |                   |                   |                   | Cohort 5    | Cohort 6    | Cohort 7    |
| Dose                  |                   |                   |                   | 400 mg twice daily | 600 mg twice daily | 800 mg twice daily |

The starting dose of 150 mg once daily in human was selected based on the information derived from nonclinical safety pharmacology and toxicology studies. This dose has been intentionally chosen as a conservative starting point to maximize safety margins according to the standard DeGeorge method, [REDACTED]

Accelerated titration (single subject per cohort) will be used for Cohorts 1 and 2 until one Grade 2 or higher at least possibly TRAE occurs during the DLT observation period (treatment cycle 1), after which another 2 subjects will be enrolled in the same cohort and the dose escalation will be converted to follow conventional 3+3 design. If no Grade 2 or higher TRAE occurs in Cohorts 1

and 2, Cohort 3 will start to follow the conventional 3+3 design. Cohorts 5 to 7 will always follow the conventional 3+3 dose escalation design.

The conventional 3+3 dose escalation will be conducted as follows:

Three subjects will be enrolled and treated in the current cohort and observed for DLT during the DLT observation period (treatment cycle 1).

- If there is no DLT, the next higher dose cohort can start.
- If there is one DLT, another 3 subjects will be enrolled and treated.
  - If there is no more than one DLT in 6 subjects, the next higher dose cohort can start.
  - If there are more than one DLTs in 6 subjects, the MTD has been exceeded and the next lower dose will be the MTD or an intermediate dose may be evaluated.
- If there are two or more DLTs, the MTD has been exceeded and the next lower dose will be the MTD or an intermediate dose may be evaluated.

This 3+3 dose escalation scheme will be repeated until the MTD is determined or the highest planned dose is reached.

Each subject will receive daily oral doses of D-1553 (once daily for Cohorts 1 to 4 and twice daily for Cohorts 5 to 7) from Day 1 to Day 21 on an empty stomach [REDACTED]

[REDACTED] Each 21-day period will be considered as 1 treatment cycle. Subjects may continue daily D-1553 until disease progression, unacceptable treatment related toxicity, withdrawal of consent or discontinuation for any reason, whichever occurs first. Safety will be assessed throughout treatment cycles and during followup periods. Dose limiting toxicity will be evaluated during the 1st treatment cycle. Pharmacokinetic parameters ( $AUC_{0-t}$ ,  $AUC_{inf}$ , MRT,  $C_{max}$ ,  $t_{max}$ ,  $C_{min}$ ,  $t_{1/2}$ ,  $V_{dss}/F$  and  $CL/F$ ) will be evaluated during the 1st and 3rd treatment cycles. PK timepoints of subsequent cohorts may be adjusted based on PK results from Cohort 1 and/or Cohort 2. Tumor assessments will be performed at screening and every 2 treatment cycles for the first 8 treatment cycles and every 3 treatment cycles thereafter until disease progression.

An SRC, [REDACTED] will regularly assess the safety of D-1553 and its combination therapy throughout the study. After completion of the 1st treatment cycle in each cohort of the conventional 3+3 dose escalation scheme, the SRC will review all available data to recommend whether or not to proceed to the next cohort. The SRC may recommend to lower the increment for the next dose level or add additional cohorts at the dose escalation meeting, based on the safety and PK results. Intermediate dose escalation levels (between Cohorts 1 and 4; Cohorts 5 and 7) may be evaluated during the study, as shown in Table 4-2.

**Table 4-2 Intermediate Dose Escalation Cohorts for Phase 1a**

| Cohorts (once daily)  | Cohort 1          | Cohort 2          | Cohort 3           | Cohort 4           |                    |                    |
|-----------------------|-------------------|-------------------|--------------------|--------------------|--------------------|--------------------|
| Dose                  | 150 mg once daily | 300 mg once daily | 600 mg once daily  | 1200 mg once daily |                    |                    |
| Intermediate Dose     | 200 mg once daily | 450 mg once daily | 900 mg once daily  |                    |                    |                    |
| Cohorts (twice daily) |                   |                   |                    | Cohort 5           | Cohort 6           | Cohort 7           |
| Dose                  |                   |                   |                    | 400 mg twice daily | 600 mg twice daily | 800 mg twice daily |
| Intermediate Dose     |                   |                   | 300 mg twice daily | 500 mg twice daily | 700 mg twice daily |                    |

At the highest dose level or MTD, the cohort may be expanded to about 10 subjects for further evaluation of safety, PK and antitumor activity. When a higher dose is determined to be safe, the previous lower dose cohort may be backfilled if further evaluation deems necessary. Subjects who completed the DLT evaluation period can receive a higher dose in subsequent cycles provided that they have tolerated the initial dose and the increased dose has been studied and proven safe. The RP2D (at or below MTD) of D-1553 as a single agent and the way it will be administered (once daily or twice daily) will be chosen based on SRC review of the safety and PK data at the completion of Phase 1a, for further evaluation in Phases 2 Arms A and B. This dose should be safe and has shown sufficient PK exposure and/or preliminary antitumor activity in Phase 1a result.

#### 4.1.2 Phase 1b (Dose Combination)

Phase 1b will determine the MTD of D-1553 in combination with [REDACTED] in subjects with advanced or metastatic [REDACTED] and other solid tumors. There are 4 groups in Phase 1b for different tumor types and combinations:

- [REDACTED]
- [REDACTED]
- [REDACTED]
- [REDACTED]

The enrollment to all groups ([REDACTED]) will occur at the same time and each group will be evaluated independently. From Phase 1a results, if the RP2D of D-1553 single agent is the same as MTD, each group will have 2 dose level cohorts of D-1553 to assess the safety and tolerability of D-1553 in combination with [REDACTED] in a conventional 3+3 design: Cohort 1 (1 dose level below RP2D of D-1553 single agent) and Cohort 2 (RP2D of D-1553 single agent). Three subjects will be enrolled in Cohort 1 first. If there is no DLT, Cohort 2 will be started. If there is 1 DLT, another 3 subjects will be enrolled in Cohort 1.

If there is no DLT in the additional 3 subjects, Cohort 2 will be started. If at any time there are more than 1 DLTs in a cohort of 3-6 subjects, the MTD has been exceeded and the next lower dose level is declared to be the MTD and safe. A dose level below Cohort 1 dose level may be added as Cohort -1 for 3+3 scheme evaluation, if Cohort 1 level is determined to be unsafe.

From Phase 1a results, if the RP2D of D-1553 single agent is lower than MTD or the MTD is not reached at the highest dose, each group in Phase 1b will start with Cohort 2 (RP2D of D-1553 single agent) in a cohort of 3 subjects to evaluate the safety and PK of combination regimens.

The SRC will review the safety and PK data (if available) of each dose cohort, after completion of the 1st treatment cycle to determine whether or not to proceed to further expansion or de-escalate to the next level. The SRC may recommend to evaluate an intermediate dose level or up to two levels lower than RP2D of D-1553 single agent, based on analysis of the safety data. Once the MTD is determined, or the RP2D of D 1553 single agent is determined to be safe with the combination regimen, that dose level group ( ) may proceed to Phase 2 in Arms F, respectively.

Each subject will receive an oral dose of D-1553 (once-daily or twice-daily) at the assigned dose, combined with cetuximab in a 21-day cycle. Subjects may continue study treatment until disease progression, unacceptable treatment -related toxicity, withdrawal of consent or discontinuation from study for other reasons, whichever occurs first.

Safety will be assessed throughout treatment cycles and follow-up periods. Pharmacokinetic parameters (AUC,  $-C_{max}$ ,  $t_{max}$ ,  $C_{min}$ ,  $t_{1/2}$ ,  $V_{dss}/F$  and  $CL/F$ ) will be evaluated during the 1st and 3rd treatment cycles. Tumor assessments will be performed at screening every 2 treatment cycles for the first 8 treatment cycles and every 3 treatment cycles thereafter until disease progression.

Once a PR or CR is observed, a confirmatory tumor assessment is recommended to be performed with at least 4 weeks' interval per RECIST 1.1.

[illegible]

#### 4.1.3 Phase 2

The Phase 2 portion is a 6-arm, parallel, open-label study to evaluate the efficacy of D-1553 single agent and combination treatments in subjects with advanced or metastatic solid tumors with KRASG12C.

The futility criteria are based on assumptions for the ORR for the SOC and the expected effect based on the addition of D-1553 to the SOC.

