#### 4.1.4 Dose Escalation and Stopping Rules

This study will evaluate the safety, tolerability, PK and efficacy of D-1553 administered as a single agent and in combination with [REDACTED] targeted therapy in subjects with advanced or metastatic solid tumors with KRASG12C mutation. In the Phase 1 part of the study, the design requires careful multiple dose level evaluations and dose escalation based on pre-set safety evaluation criteria. After the MTD or highest planned dose of D-1553 as a single agent or in combination regimen is reached, the study will go into Phase 2 evaluation to further assess the

The safety assessments for the study are accepted measures for ensuring the safety of subjects during a clinical study. The PK sampling schedule is considered appropriate given the information available from preclinical studies. The rationale for the clinical study is presented in [Section 2.7](#).

The MTD is the highest dose level of D-1553 that doesn't cause unacceptable side effects. During dose escalation in Phase 1, if 2 out of 6 subjects experience DLTs (side effects that prevent a dose increase) at a given dose level during the first cycle of the therapy, then the MTD has been exceeded and dose escalation will be stopped. The MTD will be determined as the next lower dose level. The RP2D will be at or below MTD.

[REDACTED]

[REDACTED]

[REDACTED]

[REDACTED]

- [REDACTED]
- [REDACTED]
- [REDACTED]  
[REDACTED]
- [REDACTED] [REDACTED]  
[REDACTED]
- [REDACTED]
- [REDACTED]

[REDACTED]

[REDACTED]

■ [REDACTED]  
[REDACTED]  
[REDACTED]

■ [REDACTED]  
[REDACTED]

■ [REDACTED]  
[REDACTED]  
[REDACTED] ■ [REDACTED] [REDACTED] [REDACTED] [REDACTED] [REDACTED] [REDACTED] [REDACTED]  
[REDACTED]

[REDACTED]

■ [REDACTED]  
■ [REDACTED]  
[REDACTED]

■ [REDACTED]  
■ [REDACTED]  
■ [REDACTED]  
■ [REDACTED] [REDACTED] [REDACTED] [REDACTED] [REDACTED] [REDACTED] [REDACTED]  
[REDACTED]

■ [REDACTED]  
[REDACTED]

■ [REDACTED] [REDACTED]  
[REDACTED]  
[REDACTED] [REDACTED]  
[REDACTED]  
[REDACTED]

■ [REDACTED]

■ [REDACTED]  
[REDACTED]

■ [REDACTED]

■ [REDACTED] [REDACTED] [REDACTED] [REDACTED] [REDACTED] [REDACTED] [REDACTED]  
[REDACTED]  
[REDACTED]

■ [REDACTED]  
[REDACTED]

■ [REDACTED]

■ [REDACTED]

■ [REDACTED]  
[REDACTED]

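### Phase 1b: if Cohort 1 has more than one DLT, the rule as worded declares the level below it the MTD and safe, although no subject has received that level in combination

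*Protocol*

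**What the plan says.** Protocol Section 4.1.2, repeated in the Phase 1b part of the synopsis (Section 1.1), sets up four combination groups, each judged independently. The Phase 1a result fixes where every group starts.

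- **Single-agent RP2D equal to the MTD.** A conventional 3+3 runs over two levels: Cohort 1, one level below the RP2D, and then Cohort 2 at the RP2D. The stopping sentence in this paragraph reads "If at any time there are more than 1 DLTs in a cohort of 3-6 subjects", then "the MTD has been exceeded and the next lower dose level is declared to be the MTD and safe". The sentence after it says "A dose level below Cohort 1 dose level may be added as Cohort -1 for 3+3 scheme evaluation" if Cohort 1 proves unsafe.
- **RP2D below the MTD, or MTD not reached.** Here "each group in Phase 1b will start with Cohort 2 (RP2D of D-1553 single agent) in a cohort of 3 subjects". This paragraph gives no DLT count and no rule for declaring an MTD.

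On both routes the Safety Review Committee (SRC) reviews each dose cohort after cycle 1 "to determine whether or not to proceed to further expansion or de-escalate to the next level". In addition, "The SRC may recommend to evaluate an intermediate dose level or up to two levels lower than RP2D of D-1553 single agent". Phase 2 entry is worded "Once the MTD is determined, or the RP2D of D 1553 single agent is determined to be safe with the combination regimen", after which the group may go on to its Phase 2 arm.

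Section 4.1.4 opens its definition with "The MTD is the highest dose level of D-1553" that has no unacceptable side effects. It adds that 2 DLTs in 6 subjects stop escalation and that the MTD is then the level below. Section 9.2.2 plans about 9 subjects per group over two levels, 13 in group 1, and 40 in all.

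**The concern.** The stopping sentence applies at any time and to any cohort of three to six, and it follows directly on the description of Cohort 1. Applied to a failed Cohort 1, it makes the level below Cohort 1 the combination MTD and calls it safe. No one has received that level with the combination partner; at most there are single-agent data from Phase 1a. The next sentence then treats the same level as one that may or may not be evaluated. Two adjacent sentences therefore give different answers for the same event: one settles the dose, the other leaves it to be tested if someone chooses.

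The combination MTD and RP2D are Phase 1 primary objectives (Section 3.1.1). A declared MTD also meets the Phase 2 entry condition as worded, and Arm F is planned at about 40 subjects. At stake is whether a dose can be reported as the combination MTD, and used for expansion, with no combination safety data behind it.

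**Working it through.** **1. The plan's own figure.** Three groups of 3 + 6 = 9 and one group of 3 + 10 = 13 give 3 × 9 + 13 = 40, which agrees with Section 9.2.2.

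**2. Combination subjects at the declared MTD, by route.**

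| Start (fixed by Phase 1a) | Cohort that fails | Level declared MTD | Combination subjects there | Source of the rule |
|---|---|---|---|---|
| Cohort 1 | Cohort 2, after Cohort 1 cleared | Cohort 1 | 3 to 6 | stated |
| Cohort 1 | Cohort 1 | level below Cohort 1 | 0 | stated |
| Cohort 2 directly | Cohort 2 | level below the RP2D | 0 | only if the general sentence is read across |

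The first row is sound. The second is the defect. The third depends on interpretation. Phase 1a decides the start, so the second and third rows cannot both arise.

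**3. How often a first cohort fails.** A cohort passes the 3+3 with 0 DLTs in 3, or with 1 in 3 followed by 0 in the next 3. With true DLT rate p:

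P(fail) = 1 − [(1−p)³ + 3p(1−p)² × (1−p)³]

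The protocol gives no DLT rates, so p is assumed.

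- p = 0.10: 1 − [0.729 + 0.243 × 0.729] = 1 − 0.906 = 0.094
- p = 0.20: 1 − [0.512 + 0.384 × 0.512] = 1 − 0.709 = 0.291
- p = 0.33: 1 − [0.301 + 0.444 × 0.301] = 1 − 0.434 = 0.566

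The part that occurs within the first 3 subjects is 0.028, 0.104 and 0.255. The rest (0.066, 0.187 and 0.311) comes after extension to 6.

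**4. What a test of the lower level would add.** After a failed Cohort 1 the literal rule declares the lower level every time, whatever its true DLT rate. If that level had to pass its own 3+3, it would be accepted with probability 0.60 at a true rate of 25%, 0.43 at 33%, 0.31 at 40% and 0.17 at 50% (also assumed rates).

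**5. Subjects needed if the lower level is tested.** Failed first cohort 3 to 6, plus lower level 3 to 6, gives 6 to 12. Against a plan of 9 the excess is at most 12 − 9 = 3. Against 13 in group 1 there is none (12 < 13). Cohort 2 is not opened in this case. The count covers clearing one lower level, not any later expansion there.

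**The case against.** The best defence is that the sentence was written for two planned levels. On that view the next lower level can only mean Cohort 1 after Cohort 2 has failed. If Cohort 1 fails, no lower level exists until Cohort -1 is added, and the following sentence deals with exactly that. The optional wording would then be a choice between testing a lower level and stopping the group. This is probably what was intended. It is not what the text says: the stopping sentence is not limited to Cohort 2, and the Cohort -1 sentence does not withdraw the declaration for a failed Cohort 1.

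Other points limit how far the concern reaches.

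- **Direct start.** A reader might infer that the same rule governs a failed Cohort 2 on this route. That paragraph has no DLT rule. It relies on the SRC, and de-escalating to a level ordinarily means treating subjects there.
- **Section 4.1.4.** A reader might take it as a second statement of the defect. It speaks of stopping an escalation, which presupposes a lower level already given, so it is weak support for a failed first cohort.
- **Section 4.1.1.** Its condition that a dose be studied and proven safe concerns raising the dose within a subject, not declaring an MTD. It is no real contrast.
- **Unseen text.** The contents list names a Section 4.1.5 defining the MTD and RP2D, but its heading is not visible in the body, and nearby text is redacted. A condition there cannot be ruled out. The fuller synopsis copy shows none.
- **Phase 2 safeguards.** Arm F waits for Phase 1b to be completed (Section 4.1.3), and Section 6.2.4 refers to a combination RP2D. Both point towards a tested dose, but neither requires one.

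**Conclusion.** The point holds for a failed Cohort 1: the visible rule calls a level with 0 combination subjects the MTD and safe, and testing that level is optional. On a direct Cohort 2 start, the same outcome follows only if the general sentence is read across.

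The probabilities of 0.09, 0.29 and 0.57 rest on assumed DLT rates and measure how often the unclear branch is reached. A reader might infer that Arm F is likely to open on an untested or unsafe dose. The documents do not support that: SRC review of each dose cohort is mandatory, and de-escalation is among its stated choices. The narrower conclusion is that no visible text prevents Phase 2 entry on such a dose, with the reservation about Section 4.1.5. Severity is minor to moderate: a conflict in a stated dose-finding rule, with a cheap remedy.

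**What to change.** In Section 4.1.2 and its synopsis copy:

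- Delete the words that call the next lower level safe.
- State that the next lower level is the combination MTD only if it has been cleared in combination under the existing 3+3 rule: 0 DLTs in 3, or no more than 1 in 6.
- Otherwise, require that a lower or intermediate level (for example Cohort -1) be tested in combination, or that the group be closed.
- Say that the same rule applies to a direct start at Cohort 2.
- Make Phase 2 entry depend on a dose cleared in combination.

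Check that the MTD wording in Section 4.1.4, and in 4.1.5 if it bears on this, agrees for combination cohorts.

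The cost is wording, plus 3 to 6 subjects at the lower level only in a group that de-escalates to an untested level. That is at most about 3 over the planned 9 and none over the 13 in group 1; closing the group adds none. A second lower level would add another 3 to 6. The route in which Cohort 1 clears and Cohort 2 fails needs no change and no extra subjects.
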